### Outcomes

The primary end point of the study is defined as an improvement in eHealth literacy following the implementation of the training program, scheduled to span a period of 10 weeks, as described in Textbox 2. Then, the field trials will focus on improvements in health literacy, self-efficacy, psychological well-being, and quality of life, in addition to glycemic and lipid profiles. Moreover, the study aims to minimize emotional distress and reduce body weight and BMI, as shown in Textbox 2.

For these reasons, the protocol includes study-specific questions on demographics, emotional distress, psychological well-being, and physiological aspects. All scales used in the study have been validated in the languages of the pilot sites and are deemed suitable for administration to the patients enrolled in the study. Data will be collected at baseline (T0), immediately post intervention (T1), and at the 1-month (T2) and 6-month (T3) follow-up visits, as detailed in Table 1.

### Statistical Analysis

The eHEALS score was used for sample size calculation. Specifically, the sample size was determined using the combination of a pilot study [26] and a larger study [27].

In the first case, considering a 1-tailed *t* test for paired samples in which the primary outcome eHEALS score varies from a mean of 24.3 (SD 8.9) to 28.4 (SD 8.1) [26], corresponding to an effect size of 0.48, an α error of .05 and a power of 90%, the sample size should be 39 participants. Considering a dropout rate of 15%, the sample size increases to 45 participants. While larger effect sizes reported in the literature [27] would suggest even smaller sample sizes, we decided to include 200 participants for several reasons: (1) to ensure robust and generalizable results across a diverse population of older adults with type 2 diabetes, (2) to account for potential variability in baseline eHealth literacy and other characteristics, (3) to maintain statistical power for secondary outcomes and subgroup analyses, and (4) to address existing gaps in the literature by providing sufficiently powered evidence on the efficacy of the intervention.

The initial phase of the data analysis will entail the description of the sample. Continuous variables will be reported as either the mean and SD or the median and IQR on the basis of their distribution (assessed using Kolmogorov-Smirnov test). Categorical variables will be expressed as an absolute number and percentage. In the context of group comparisons, continuous variables will be compared using independent or 2-tailed paired *t* tests for normally distributed data and Mann-Whitney *U* or Wilcoxon signed-rank tests for nonnormally distributed data, whereas categorical variables will be compared using chi-square or Fisher exact tests, as appropriate. A significance level of *P*<.05 will be applied. Corrections for multiple comparisons (eg, the Bonferroni or Holm method) will be applied where necessary. The results will be compared with the data from the other partner countries. Descriptive statistical analyses will be performed on the quantitative data with SPSS software (version 29.0.1.0; IBM Corp) or Rstudio (version 4.4.1; Posit PBC).

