**Objective:**

This pilot study aims to evaluate the effectiveness of a structured, 5-week training program in improving eHealth literacy among older adults with type 2 diabetes and to assess its impact on health literacy, self-efficacy, psychological well-being, and clinical outcomes.

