**Methods:**

In total, 200 community-dwelling adults aged ≥60 years with type 2 diabetes, a Mini-Mental State Examination score ≥24, a Geriatric Depression Scale score <9, and a low eHealth Literacy Scale score (≤29) will be recruited. Participants will attend five 90-minute weekly training sessions combining didactic and interactive modules focused on health literacy, diabetes self-management, and the use of digital tools. Assessments will be performed at baseline (T0), post intervention (T1), and at 1-month (T2) and 6-month (T3) follow-up. The primary outcome will be the change in eHealth literacy, as measured by the eHealth Literacy Scale, from baseline to post intervention. In addition, a wide range of secondary outcomes will be examined to capture the program’s multidimensional impact: improvements in general health literacy, self-efficacy in diabetes management, psychological well-being, and quality of life; reductions in diabetes-related emotional distress, body weight, and BMI; and better metabolic control, as measured by hemoglobin A_1c_ and lipid profiles. Finally, participants’ experiences, satisfaction, and perceived benefits will be explored to inform the future scalability and refinement of the program. A prestudy will be conducted, involving stakeholders, older adults, and caregivers, to refine the training content using co-design techniques. Descriptive statistics will be used to summarize sample characteristics. Preintervention and postintervention changes will be evaluated using 2-tailed paired *t* tests or their nonparametric equivalents, with repeated-measures models applied to follow-up data. A *P* value <.05 will indicate statistical significance.

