## Methods

### Field Trial

The JACARDI trial is a multicenter study coordinated by the Istituto di Ricovero e Cura a Carattere Scientifico-Istituto Nazionale di Riposo e Cura per Anziani (IRCCS INRCA) and conducted also at the Clinic of Endocrinology and Metabolic Diseases of the Azienda Ospedaliero-Universitaria delle Marche. Adopting a blended approach combining didactic and interactive training, the study primarily aims to improve eHealth literacy in older adults with type 2 diabetes, thereby promoting independent living and reducing the risk of health deterioration and impaired quality of life. The study consists of five phases: (1) recruitment and screening, (2) baseline assessment (T0), (3) a 10-week educational intervention, (4) postintervention assessment (T1), and (5) follow-up evaluations at 1 month (T2) and 6 months (T3).

Prior to the trial, a prestudy will be conducted to co-design and finalize the training content. A group of volunteers whose characteristics are similar to those of the target population will participate in focus groups to refine the training content and practical aspects prior to recruitment. The protocol was developed in accordance with the SPIRIT guidelines (Checklist 1).

Figure 1 shows the design of the JACARDI study.

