**Exclusion criteria**
Failure to meet the inclusion criteriaSimultaneous participation in other studiesLack of written informed consentHistory of a myocardial infarction or stroke within the past 6 monthsPainful arthritis, spinal stenosis, amputation, painful foot lesions, or neuropathy, limiting balance and mobilityUncontrolled hypertensionAdvanced Parkinson disease or other neuromuscular disorderDiagnosis of metastatic cancer or treatment with immunosuppressive therapySignificant visual or hearing impairment

Following the medical visit, the investigator will contact the potential participant by email or telephone to discuss the study and confirm their interest in participation. At this stage, detailed information about the study procedures will be provided, and written informed consent will be obtained before any study-related activities are initiated. The schedule for the visits and the procedures for conducting the research at the participant’s home will then be agreed upon according to participant availability. When recruitment is complete, participants included in the study will undergo all routine clinical investigations, such as collection of blood samples to assess their glycemic and lipid profiles and measurement of BMI. In addition, a researcher will perform the preliminary evaluation (T0). The scales described in Textbox 2 will be administered, and then an interview will be conducted. The participant will undergo training sessions at the study centers with the other study participants. After 10 weeks, the final evaluation will be conducted (T1). Participants will be required to complete a series of questionnaires, the details of which can be found in Table 1. During this phase, blood sample collection and BMI measurement will not be performed.

During the 2 follow-up visits (1 month and 6 months following the conclusion of the intervention), any alterations in the patient’s medical history will be recorded. All routine clinical investigations and all planned assessment scales will be administered. Blood sample collection to assess the glycemic and lipid profiles and BMI measurement will be performed exclusively at T3.

Textbox 2.Outcomes of the study.

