## Results

The recruitment process is scheduled to start in September 2025 and will continue until September 2026. The prestudy phase, aimed at evaluating the core concepts, strategies, and format designed for conducting the pilot study and refining the training content, began in April 2025. The rating scales used are shown in Table 1, grouped by study phase. Improvements in both health literacy and eHealth literacy are expected to be observed among participants, as assessed through validated instruments administered before and after the intervention. Enhancements in diabetes self-management behaviors, such as medication adherence, dietary habits, and glucose monitoring, are also anticipated. Moreover, an increased level of literacy is expected to result in greater self-efficacy and confidence in the use of digital health tools. Positive changes in psychosocial outcomes, including quality of life, perceived autonomy, and reduction in diabetes-related distress, are also expected. These outcomes will be systematically evaluated as part of the JACARDI study, providing comprehensive evidence on the effectiveness of the intervention and its impact on the health literacy, self-management, and psychosocial well-being of older adults.

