From a methodological point of view, the study adopts a robust evaluation framework using validated tools and multiple follow-up time points, thereby enabling both short-term and midterm outcome monitoring. The use of both subjective (eg, questionnaires) and objective (eg, glycemic and lipid profiles) measures allows for a multidimensional evaluation of the intervention’s impact.

However, it is important to acknowledge some limitations. This being a pilot study, the generalizability of the results may be constrained by the specific characteristics of the local settings and participants. Moreover, despite efforts made to personalize the intervention, its scalability across different health care systems and sociocultural environments may require further adaptations. Potential barriers include disparities in digital access or digital literacy among older adults, as well as local infrastructure constraints that may affect intervention delivery. To address these issues, the study will employ a blended training format combining digital and in-person components and provides technical support and guidance to participants. Feedback will be collected to inform future adaptations for broader implementation. In addition, the exclusion criteria—particularly the exclusion of individuals with severe mobility limitations, advanced Parkinson disease, and significant visual or hearing impairment—may restrict the external validity of the findings. The establishment of these criteria was deemed necessary to ensure the attendance of all participants to the requisite training sessions and to facilitate their effective engagement with the digital tools that will be introduced. Nevertheless, they also exclude subgroups that may be among the most vulnerable to poor digital health engagement. It is recommended that future studies consider tailored strategies (eg, home-based or caregiver-assisted training, accessible digital interfaces) to reach these populations and evaluate whether adapted interventions can address their specific needs.

Despite these challenges, the JACARDI pilot study represents a valuable contribution to the growing field of digital health literacy and chronic disease self-management.

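### The sample size is justified as powering efficacy, but with no untrained group the design has power only for within-person change

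*Protocol article*

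**What the plan says.** The sample size paragraph (Protocol article, Statistical Analysis) derives 39 participants, or 45 with dropout, from a paired t test on eHEALS. It then raises the number to 200 for four reasons, the last of which includes "providing sufficiently powered evidence on the efficacy of the intervention". The abstract objective is to evaluate "the effectiveness of a structured, 5-week training program", and the Results section expects the study to end up "providing comprehensive evidence on the effectiveness of the intervention".

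The design has one group. The abstract states: "Participants will attend five 90-minute weekly training sessions combining didactic and interactive modules". The Field Trial section states: "The study consists of five phases: (1) recruitment and screening, (2) baseline assessment (T0), (3) a 10-week educational intervention", followed by T1 and the two follow-ups, with no comparator phase or arm. The Participant Recruitment section confirms shared group delivery: "The participant will undergo training sessions at the study centers with the other study participants". On the endpoint, the abstract says: "The primary outcome will be the change in eHealth literacy, as measured by the eHealth Literacy Scale, from baseline to post intervention", to be tested with paired tests, with repeated-measures models for follow-up.

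Textbox 1 makes eHEALS of 29 or less an entry criterion. Table 1 marks eHEALS at recruitment, T1, T2 and T3, but not at T0. The text after Textbox 1, however, says that the Textbox 2 scales, which include eHEALS, are administered at T0.

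The limitations in the Discussion say that "generalizability of the results may be constrained by the specific characteristics of the local settings and participants" and go on to scalability, digital access and the exclusion criteria. They do not mention the lack of a control group.

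**The concern.** Power is always power for a particular contrast. Here the contrast is each participant's later score against their own earlier score, so the high power is for the statement that mean change is not zero. Efficacy is a statement about training against no training, and no described analysis estimates that difference. Adding participants narrows the interval around the before-after change but does not remove what else is in it: regression to the mean, repeated completion of the same self-report scales, and concurrent care. HbA1c, lipids and weight are compared between T0 and the last follow-up, so months of routine diabetes care fall inside that change.

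This trial is more exposed than most single-group studies because participants are selected for low values of the primary outcome. If the selecting score is also the baseline, some upward change is expected with no intervention at all. The Discussion makes replication conditional on the approach proving effective, so an overclaim would carry into later decisions.

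**Working it through.** **1. Reproducing the plan's figure.** Inputs from Statistical Analysis: eHEALS 24.3 (SD 8.9) to 28.4 (SD 8.1), effect size 0.48, one-tailed α 0.05, power 90%, dropout 15%.

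- Mean change: 28.4 − 24.3 = 4.1.
- SD of change, assuming a pre-post correlation of 0.5: √(8.9² + 8.1² − 2 × 0.5 × 8.9 × 8.1) = √72.73 = 8.53. Then 4.1 / 8.53 = 0.48, as stated.
- Paired t test (noncentral t), one-sided: n = 39, power 0.903. This reproduces.
- Dropout: 39 × 1.15 = 44.85, so 45 as stated; 39 / 0.85 = 45.9 would give 46. The difference is trivial.

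The arithmetic is not in dispute.

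**2. What 200 participants buy.** Evaluable: 200 × 0.85 = 170. The two-sided paired test at 0.48 then has power above 99.99%, and a mean change of 0.25 SD (0.25 × 8.53 ≈ 2.1 points) is detectable with 90% power. Both figures concern change against zero.

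**3. Is there an untrained group anywhere?**

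| Planned analysis | Untrained group described? |
|---|---|
| Paired t or Wilcoxon signed-rank test | No, own earlier value |
| Repeated-measures models | No, own earlier values |
| Independent t, Mann-Whitney, chi-square, Fisher | No, the groups are not identified |
| Comparison with partner countries | No, not described as untrained |

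**4. Regression to the mean with zero training effect.** Assumptions, since the article does not give these figures: normal eHEALS scores in the source population, mean μ = 24.3 and SD σ = 8.9 (borrowed from the sample size inputs), test-retest correlation ρ, and the screening score used as baseline.

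- Cutoff: b = (29 − 24.3) / 8.9 = 0.528.
- Mean shortfall of those selected: σ × φ(b)/Φ(b) = 8.9 × 0.347 / 0.701 = 4.40 points below μ.
- Expected gain at retest: (1 − ρ) × 4.40. For ρ = 0.9 this is 0.44 points; for ρ = 0.5 it is 2.20.
- Against the planned 4.1: 0.44 / 4.1 ≈ 11% and 2.20 / 4.1 ≈ 54%.

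If the source population mean were 28 instead, the simulated gain is 0.65 to 3.25 points.

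**5. Effect of sample size on a false positive.** Simulated with zero training effect (2000 runs per setting, two-sided paired t test, μ = 24.3), share of trials declaring improvement:

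| n | ρ = 0.9 | ρ = 0.7 | ρ = 0.5 |
|---|---|---|---|
| 45 | 11% | 25% | 41% |
| 170 | 31% | 70% | 92% |
| 200 | 35% | 80% | 97% |
| 1000 | 95% | 100% | 100% |

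Any other non-specific drift behaves the same way. A drift of 1 point with SD of change 8.53 is significant in 12% of trials at n = 45, 33% at n = 170 and 96% at n = 1000.

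**The case against.** The strongest defence is that this is called a pilot throughout, that a single-group pilot is a legitimate design, and that the primary outcome is honestly defined as change after training. The Discussion also says that further research is needed on clinical effectiveness, and changes in medical history are recorded at both follow-ups. All of that stands, and the design itself is not the fault. It does not rescue the sample size paragraph, which goes beyond a pilot by naming powered efficacy evidence as a reason for the number chosen. Recording medical history may help interpretation but supplies no contrast.

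Four stronger readings are tempting, and the article does not support them:

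- A reader might infer that only before-after tests are planned. Independent-group tests, repeated-measures models and a partner-country comparison are also listed. The point is that none is described as having an untrained group.
- A reader might infer that the screening score is certainly the baseline. Table 1 implies it, but the Participant Recruitment text implies a T0 measurement.
- A reader might infer that the trial must add a concurrent control, for example by delaying the start for some participants. That is a design preference. The article gives a recruitment window but no training calendar, so feasibility cannot be judged from it.
- A reader might infer that an observed gain would be mostly artefact. The figures above depend on assumed correlations and an assumed source population; they show what is possible, not what will happen.

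Figure 1 is not available, but its caption mentions screening, intervention, follow-up and the final sample, and no arms.

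**Conclusion.** The concern holds as a mismatch between a stated property and the design. The plan claims power for efficacy and evidence on effectiveness; what it has, at any sample size, is power to show that mean within-person change is not zero. The conclusion itself rests only on the article's text.

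Its size is illustrative. Under the stated assumptions, regression to the mean alone could account for about 0.4 to 2.2 of the planned 4.1 points, and at 170 evaluable participants the paired test would declare improvement in roughly 31% to 92% of trials with no training effect. These figures apply if the screening score is the baseline; a separate T0 score would remove much of this component, but not repeat testing or concurrent care. The sample size arithmetic is sound, and 200 is ample for the paired test. Choosing 200 rather than 45 does not address the problem and makes a false attribution more likely. The limitations section should have named this and does not.

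**What to change.** 1. In Statistical Analysis, restate the fourth reason for 200 participants as adequate power for within-person change in eHEALS after training. Reword the effectiveness claims in the abstract objective and the Results section to match.
2. In the Discussion limitations, add the absent control group, regression to the mean arising from the entry rule of 29 or less, repeat testing, and concurrent care.
3. State that changes in HbA1c, lipids and weight will not be attributed causally to the training.
4. Reconcile Table 1, which shows no eHEALS at T0, with the Participant Recruitment text, which has the Textbox 2 scales administered at T0. If eHEALS is measured at T0, use that score rather than the screening score as baseline, and report the untreated change from recruitment to T0 beside the change from T0 to T1.

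Items 1 to 3 are wording only; their cost is a less favourable claim. Item 4 adds one descriptive contrast and, if Table 1 is what governs, one extra short questionnaire at T0. No additional participants are needed.

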The training sessions will be facilitated by a multidisciplinary team of health care professionals and educators with expertise in diabetes management, health literacy, and digital health. The trainers will generally include doctors, nurses, dietitians, and clinical psychologists, each with previous experience in patient education and group facilitation. At each center, depending on the staff present and the topic of the session, the facilitators may vary.

To ensure consistency and fidelity across sessions and locations, the coordination center will be responsible for the preparation of all training materials, including manuals, slides, and practical exercises. These materials will be disseminated to all locations before the program begins. In addition, online and in-person familiarization sessions will be conducted for all trainers to review content, clarify any questions, and practice delivering the modules. This will ensure that all trainers are familiar with the course materials. Trainers will also receive guidance on specific strategies for addressing particular issues, such as managing emotional challenges or promoting autonomy, to maintain a supportive approach throughout the program. These sessions are designed to ensure that training is conducted in the same way across all centers, while still allowing trainers to adapt to the needs of participants.

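### Training is delivered in groups, but the Statistical Analysis section names only participant-level tests and omits the repeated-measures models that the Abstract promises for follow-up

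*Protocol article*

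**What the plan says.** The Statistical Analysis section gives this rule for continuous measures: "compared using independent or 2-tailed paired *t* tests for normally distributed data and Mann-Whitney *U* or Wilcoxon signed-rank tests for nonnormally distributed data". It names no longitudinal model and no term for training group or centre, and the sample size contains no design effect.

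The Abstract (Methods) names the same kind of test for the primary comparison: "Preintervention and postintervention changes will be evaluated using 2-tailed paired *t* tests or their nonparametric equivalents". It then adds "with repeated-measures models applied to follow-up data". That second element does not appear in the Statistical Analysis section, although the Outcomes section plans assessments at baseline, T1, T2 and T3.

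On delivery, Participant Recruitment says: "The participant will undergo training sessions at the study centers with the other study participants". The same section refers to in-person group sessions. Under Intervention Through Training, Modules I and II include group discussions, and at each centre, "depending on the staff present and the topic of the session, the facilitators may vary".

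**The concern.** People who sit in the same sessions share facilitators, discussion and group dynamics, so their changes in eHEALS may resemble each other more than those of people in different groups. A paired t test or a Wilcoxon signed-rank test on about 200 individual changes assumes that no such resemblance exists. If it does exist, the standard error of the mean change is understated, the confidence interval is too narrow and the stated significance level is not the true one. The same applies to the secondary scales and subgroup analyses, which the article cites among its reasons for choosing 200 participants.

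A second, separate gap is that a reader of the Statistical Analysis section cannot tell how T2 and T3 will be analysed, because the models promised in the Abstract are absent there.

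**Working it through.** **Inputs from the article (Statistical Analysis).** The calculation is described as "considering a 1-tailed *t* test for paired samples", with eHEALS moving from 24.3 (SD 8.9) to 28.4 (SD 8.1), effect size 0.48, and "an α error of .05 and a power of 90" percent. The stated sizes are 39, then 45 after 15% dropout, with 200 planned.

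**The article's own figure.** Exact noncentral-t power for a paired test with standardised change 0.48, one-sided 0.05 and 90% power gives n = 39, which matches. The inflated figure matches 39 × 1.15 = 44.85, so 45; dividing instead, 39 / 0.85 = 45.9, gives 46, a trivial difference. The 2-tailed test that the analysis names needs 48. None of these figures allows for clustering.

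**Inputs that the article does not give.** Group size m and the ICC of the change score. I assume m = 10 to 20 and ICC = 0.02 to 0.05. Completers: 200 × 0.85 = 170.

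**Design effect**, DE = 1 + (m − 1) × ICC:
- m = 10, ICC 0.02: 1 + 9 × 0.02 = 1.18
- m = 20, ICC 0.05: 1 + 19 × 0.05 = 1.95

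**Interval width**, multiplied by √DE: √1.18 = 1.09 and √1.95 = 1.40, so 9% to 40% wider. In eHEALS points, the SD of change implied by the article is 4.1 / 0.48 = 8.54. The participant-level 95% half-width is 1.96 × 8.54 / √170 = 1.28. Multiplied by √DE, it becomes 1.39 to 1.79. With groups of 20 there would be only about eight groups (170 / 20 = 8.5), so a proper small-sample correction would widen it further.

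**Actual two-sided error of a nominal 5% test**, 2 × [1 − Φ(1.96 / √DE)]:
- DE 1.18: 1.96 / 1.086 = 1.80, giving 0.071
- DE 1.95: 1.96 / 1.396 = 1.40, giving 0.160

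**Effective sample size**, 170 / DE: 144 and 87.

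**Power at 0.48, two-sided.** Above 99.9% with 170 independent changes, and about 97% at m = 20, ICC 0.05, using a t test on group means. The number to recruit there is 48 × 1.95 = 93.6, so 94; then 94 / 0.85 = 110.6, so 111, which is below 200.

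**Sensitivity to the assumption.** For ICC 0.01 to 0.10 with the same group sizes, DE is 1.09 to 2.90, the actual error about 6% to 25%, and power about 88% or more. Only at ICC 0.20 with groups of 20 (DE 4.8) does power fall to about 69%.

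**The case against.** The strongest reply is that the size of the problem is wholly assumed. With an ICC of zero the named tests are valid, and the article does reduce variation between groups: materials are prepared centrally and trainers attend familiarisation sessions. In a single-arm pilot with far more participants than its calculation requires, the primary conclusion is unlikely to change. All of this stands, and it makes the concern conditional. It does not remove it, because trainers may still adapt to participants, facilitators vary, and the article names tests that cannot reflect any within-group correlation. Nor is this merely detail left to an analysis plan, since the article itself specifies participant-level tests.

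Four stronger readings are tempting but not supported:

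- **That the Abstract contradicts the primary test.** It does not. Both places name a 2-tailed paired t test or its nonparametric counterpart for the pre-post change. The mismatch is an omission about follow-up data.
- **That the eHEALS eligibility limit of 29 forces a switch to Wilcoxon.** A paired test depends on the distribution of the change, not of the truncated baseline score, and the Kolmogorov-Smirnov check is tied explicitly only to descriptive reporting. What remains is a preference for fixing the primary test in advance.
- **That dropout biases the primary result.** A paired test would exclude about 30 of 200 people (200 × 0.15), but no missing-data rule is stated and it may sit elsewhere. A mixed model mainly recovers people with partial follow-up; someone with baseline only adds little to the T1 contrast.
- **That the categorical tests are wrong.** The section says "categorical variables will be compared using chi-square or Fisher exact tests, as appropriate" in the context of group comparisons, and no paired categorical endpoint is specified.

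**Conclusion.** The point holds in a conditional form and should be addressed. Group delivery is documented, the named tests assume independent changes, and the Statistical Analysis section lacks the follow-up models given in the Abstract. If change is positively correlated within training groups, reported precision will be overstated: intervals should be about 9% to 40% wider, and a nominal 5% test would run at about 7% to 16%. Those figures rest on assumed groups of 10 to 20 and an ICC of 0.02 to 0.05, neither of which is in the article. A reader might infer that the trial is underpowered or that its error rate is certainly inflated. Neither follows: primary power stays at about 97% or more in this range, and any inflation depends on a positive ICC.

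**What to change.** - Record a training-group identifier for every participant as groups form, since it may be hard to reconstruct later.
- In both the Abstract and the Statistical Analysis section, name one linear mixed model for eHEALS over the baseline, T1, T2 and T3 assessments (Table 1 places the baseline eHEALS at recruitment). Use visit and centre as fixed effects, a random effect for participant, and a training-group random effect that lets the change vary by group. Cluster-robust standard errors with a small-sample correction would be an equivalent choice. Use all available data.
- Make the mean T1 minus baseline change, tested 2-tailed at .05, the primary contrast whatever a normality test shows, with the Wilcoxon signed-rank test as a sensitivity analysis.
- Use the same model for the secondary scales.

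The cost is analysis wording and one data field. The downside is a somewhat wider interval if groups do differ. No change to the sample size is called for under the assumptions used here.
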